**Methods:**

A total of 100 participants (aged 19-25 years) from the National University of Singapore will be recruited and randomized into 2 arms. In arm 1 (n=50), the seekers will use Acceset with befrienders (n=30) as well as moderators (n=30) for 3 weeks. Arm 2 comprises a wait-listed control group (n=50). A questionnaire battery will be used to monitor seekers and befrienders at 4 time points. These include baseline (before the intervention), 3 weeks (end of the intervention), and 6 and 9 weeks (carryover effect measurement). Implementation outcomes of the intervention will involve evaluation of the training curriculum with respect to adoption and fidelity as well as user acceptability of the Acceset platform and its feasibility for broader deployment. Clinical outcomes will include mattering, selfhood, compassion, mindfulness, perceived social support, and psychological well-being scores.

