**Aims and hypotheses**
Aim 1: the first aim is to evaluate the implementation effectiveness of digital peer support training between emerging adults providing support (befrienders) and emerging adults seeking help (seekers).Research question 1a: is Acceset digital peer support training an effective training curriculum in providing peer support?Hypothesis 1a: the digital peer support training is effective for befrienders in providing peer support, as demonstrated by the adoption of and fidelity to the training curriculum.Research question 1b: is the Acceset text-based intervention (ie, the platform) feasible and acceptable (ie, safe and timely) as an ongoing mechanism of support for seekers and befrienders?Hypothesis 1b: digital peer support is feasible and acceptable in offering support for emerging adults’ mental well-being, which is evidenced by 2 indicators:The engagement of the seeker-befriender-moderator interaction across the 4 time points—baseline (before the intervention), 3 weeks (conclusion of the intervention), and 6 and 9 weeks (carryover effect assessment)—that is indexed by the waiting period for seekers to receive a response. Delays are defined as a >48-hour waiting period and will be categorized based on the following reasons: (1) technical factors (eg, the befriender is not able to log into the platform to respond in time) and (2) human factors (eg, the befriender drops out from the study, and no replacement is found in time). An acceptable response time is within 48 hours, and this is emphasized during Acceset digital peer support training for befrienders [37].The use of technical features of the Acceset platform that is measured by the seeker dropout rate at each stage of engagement with the Acceset platform, the number of visits on the study registration website, the number of participants who registered with Acceset, the average number of letters exchanged, and the average number of emotion and functional adjustment stickers and motivation graphic interface formats used [37].Research question 1c: is the Acceset text-based intervention (ie, the platform) feasible and acceptable (ie, safe and timely) as an ongoing mechanism of support that identifies individuals who are at an unacceptably high risk of mental health conditions?Hypothesis 1c: digital peer support is feasible and acceptable in offering support for emerging adults’ mental well-being by identifying individuals who are at an unacceptably high risk of mental health conditions related to depression and suicidality, which is measured before and during engagement based on 3 means—specifically, the Acceset algorithm detection of the content of the letters, the moderators’ vetting of the content of seekers’ letters, and the seekers’ self-report responses to the 9-item Patient Health Questionnaire [38] (refer to the Implementation Outcomes section for details [37]).Aim 2: the second aim is to elucidate whether Acceset digital peer support harnesses the 4 components of emerging adult mental health—mattering, selfhood, compassion, and mindfulness.Research question 2a: does Acceset digital peer support enhance the 4 components among seekers and befrienders?Hypothesis 2a: Acceset digital peer support (training) increases the 4 components among befrienders (before and after training) and seekers (over the course of the study across 4 time points).Research question 2b: is Acceset digital peer support effective in improving emerging adult mental well-being?Hypothesis 2b: digital peer support leads to significantly better mental well-being of seekers compared with the control group. This effect is sustained beyond the period of the intervention.Aim 3: the third aim is to investigate the mechanism of change in emerging adult mental well-being involving digital peer support (delivered by the Acceset platform).Research question 3: what is the mechanism explaining the change in emerging adult mental well-being involving digital peer support?Hypothesis 3: the initial level and rate of change (ie, growth factors) of befrienders’ web-based support positively predict the growth factors of seekers’ psychological well-being in accordance with latent growth curve modeling.

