#### Clinical Outcomes

To address research question 2a and hypothesis 2a, we will examine whether the Acceset training curriculum can enhance the 4 components of psychological well-being among befrienders and seekers. We will compare the change in mattering, selfhood, compassion, and mindfulness scores of befrienders between baseline and following Acceset training (ie, before vs after training) and those of seekers over the course of the study. As for research question 2b and hypothesis 2b, we hypothesized that engagement with Acceset digital peer support will lead to improved mental well-being of the seekers compared with the control group and that this effect may be sustained beyond the period of the intervention. To assess these effects, we will evaluate the change in mental well-being of the participants in both study groups (intervention and control) after 3, 6, and 9 weeks from baseline using self-report questionnaires. Seekers will provide responses pertaining to help-seeking behavior beyond the Acceset platform at weeks 6 and 9 using the perceived social support measure in the questionnaire battery. We will assess the correlations of the 3 digital features—comprising emotion and functional adjustment stickers and motivation GIFs, which reflect seekers’ mental well-being during engagement with the platform—with their well-being scores from the questionnaires.

The scale or set of scales used to assess the clinical outcomes, including the 4 components of psychological well-being underpinning the Acceset training curriculum, measures of seekers’ well-being, and perceived social support, are outlined in the following paragraph.

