### Data Collection, Management, and Analyses

Acceset will serve as the data collection platform. Participants (both seekers and befrienders) will initially enter their details on the sign-up page, which includes role preference (seeker, befriender, or either), email, date of birth, gender, nationality, ethnicity, monthly household income, and password. The user will be required to answer the PHQ-9 to determine their eligibility. An email will also be sent to the users’ registered email address for verification. Once eligible individuals are selected and assigned their respective roles, they will be given a unique nonidentifying ID to participate in the study. Participants’ self-reported questionnaire responses at each time point and the digital letter exchange content will be securely stored and tied to their specific IDs. The data collected will be stored on the cloud servers of the leading author’s affiliated institution. Once the research concludes, the information will be downloaded to a Microsoft Excel sheet, and all personal information will be deidentified for data analyses.

A power analysis assessed the adequate sample size needed for the RCT to have sufficient power to detect valid effects. The intervention (n=50) and control (n=50) arms were derived from multiple dependent variables assessing implementation testing (ie, feasibility and utility) and clinical outcomes. To address any potential challenges with missing data, the Little Missing Completely at Random Test will address potential missing data via full information maximum likelihood imputation [37,59]. Maximum likelihood estimation is a method that ascertains the parameter values of a model using the mean and variance and maximizes the chance that the values generated are closest to those observed.

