The following approaches will be used for data analysis and interpretation. Independent-sample 2-tailed *t* tests will compare the intervention and control groups. Bonferroni post hoc tests will control for multiple comparisons. For both the intervention and control groups, additional independent *t* tests will compare seekers who provided data across all 4 time points with those who dropped out from the study for different reasons to ascertain if the sample with data across all 4 time points and the sample with fewer data points bias our results. For instance, seekers may drop out when risk assessments identify them as having a high risk of depression and suicidality during the course of the study. There will also be instances when befrienders discontinue the letter writing because of the sensitive nature of the letter content that may cause distress and befrienders not being fully comfortable, and the system will inform the seekers and obtain their consent to end the letter thread instead of continuing the conversation with a new befriender. Second, each participant’s emotional experiences disclosed on Acceset will be extracted based on the definitions of the 4 components of psychological well-being. Latent Dirichlet allocation analyses in R (R Foundation for Statistical Computing) and content analysis will be used [37,60,61].

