## Results

This protocol received approval from the Institutional Ethics Review Board of NUS in October 2021. Recruitment will commence in January 2022. Data collection began in March 2022 and was completed in June 2022. Data analysis started in July 2022 and is currently in progress. We aim to report the preliminary study outcomes in December 2022. The effect size will be analyzed using the Cohen *d* index with a significance level of .05 (95% reliability) and 80% power statistic [37]. A total of 100 seekers, 35 befrienders, and 2 moderators were recruited in January 2022.

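### Holm's step-down procedure over the same family would replace single-step Bonferroni at no cost in error control, and the family should be named

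*Protocol article*

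**What the plan says.** In the protocol article, Data Collection, Management, and Analyses states: "Independent-sample 2-tailed *t* tests will compare the intervention and control groups". The next sentence is the whole of the multiplicity plan: "Bonferroni post hoc tests will control for multiple comparisons". No family is defined there or elsewhere in the article.

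The comparisons that could fall under it are described in other sections:
- The Methods paragraph of the Abstract lists six domains: "Clinical outcomes will include mattering, selfhood, compassion, mindfulness, perceived social support, and psychological well-being scores".
- Clinical Outcomes sets the comparison of the two groups "after 3, 6, and 9 weeks from baseline using self-report questionnaires".
- Hypothesis 2b in Textbox 1 says seekers will do better than controls and adds: "This effect is sustained beyond the period of the intervention". Clinical Outcomes is softer and says only that the effect may last.

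On size, "The intervention (n=50) and control (n=50) arms were derived from multiple dependent variables". The Results section ties the effect size to Cohen's d "with a significance level of .05 (95% reliability) and 80% power statistic", gives no value of d and mentions no corrected level. The same section reports that data collection ended in June 2022 and that analysis began in July 2022.

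**The concern.** Single-step Bonferroni tests every one of k comparisons at .05/k, however many of the others are already significant. Holm starts at the same level and relaxes it after each rejection. It needs no further assumption about how the tests are correlated and no ordering of outcomes or weeks. For accept-or-reject decisions, then, single-step Bonferroni gives up power without a gain in error control.

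This matters most where one outcome should show a difference at more than one week, as with a claim that a benefit appears and then lasts. With 50 per arm there is little power to spare.

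**Working it through.** **Inputs from the article.** 50 per arm; two-sided tests; alpha .05; three follow-ups (weeks 3, 6, 9); six named outcome domains.

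**Inputs assumed, because the article gives none.** d = 0.5 (range 0.3 to 0.8); correlation 0.6 between weeks and 0.5 between outcomes; no dropout; normal approximation. The family is shown as one, two or six outcomes by three weeks, so k = 3, 6 or 18.

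**Step 1: the plan's own figure.** The 50 per arm cannot be reproduced without an effect size. Solving backwards, the difference detectable with 80% power at unadjusted .05 is d = (1.960 + 0.842) × √(2/50) = 2.802 × 0.2 = 0.56.

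**Step 2: power per test under Bonferroni.** The expected test statistic is d√(n/2) = 0.5 × √25 = 2.5, and power is about Φ(2.5 − z).
- Unadjusted: z = 1.960, Φ(0.540) = 71%.
- k = 3: level .0167, z = 2.394, Φ(0.106) = 54%.
- k = 6: level .0083, z = 2.638, Φ(−0.138) = 45%.
- k = 18: level .0028, z = 2.991, Φ(−0.491) = 31%.

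**Step 3: why Holm rejects at least as much.** Order the p values. Compare the smallest with .05/k, the next with .05/(k − 1), and so on, stopping at the first failure. Every threshold is at least .05/k, so whatever Bonferroni rejects Holm rejects too. With three invented p values of .010, .020 and .040, Bonferroni (.0167 each) rejects only the first. Holm (.0167, .025, .05) rejects all three.

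**Step 4: simulated gain** (100,000 runs of correlated z statistics, d = 0.5 at every week).

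| Outcomes × weeks | All three weeks for an outcome: Bonferroni | Holm | Single week: Bonferroni | Holm | Familywise error, global null (both rules) |
|---|---|---|---|---|---|
| 1 × 3 | 32% | 48% | 54% | 62% | 4.2% |
| 2 × 3 | 23% | 38% | 45% | 54% | 4.0% |
| 6 × 3 | 13% | 23% | 31% | 39% | 3.9% |

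The first Holm step is the Bonferroni step, so the chance of at least one rejection is the same for both rules (76% in the first row). All the gain comes after the first rejection.

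**Step 5: sensitivity to d** (one outcome, all three weeks). At d = 0.3 the figure rises from about 5–6% to 12%. At d = 0.8 it rises from 88% to 95%.

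**Step 6: ordered testing, for comparison** (one outcome, each week at .05, a later week tested only if the earlier one is significant).
- d = 0.5 at every week: week-3 power is 71% against 54% for Bonferroni, but week-9 power is about 50% against 54%. Holm gives about 62% at week 9.
- d = 0.2 at week 3 and 0.5 afterwards: week-6 power falls from 54% (Bonferroni) to 16%. Holm gives 58%.

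**The case against.** Bonferroni controls familywise error and is a legitimate choice. The article does not state it wrongly, and a condensed article may leave the family to a fuller plan. That stands: this is a point of efficiency, not an error.

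Several stronger readings are tempting, and the article does not support them.
- **That the correction spans all outcomes and all three follow-ups.** The article never says so. The sentence could also refer to comparisons among the four time points in hypothesis 2a, so the term post hoc cannot be called meaningless. The Holm point does not depend on the family, provided that it holds at least two tests.
- **That hypothesis 2b fixes a testing order, so that gating weeks 6 and 9 behind week 3 is free.** The wording fits such an order over time but does not prescribe one. Clinical Outcomes says only that the effect may be sustained, and the growth-curve analysis compares linear, quadratic and other shapes, which leaves the time course open. Step 6 shows that the order costs power for late effects and can fall below Bonferroni at week 9.
- **That a sustained effect requires significance at all three weeks.** No section says this. It is used here only as a convenient measure of the gain.

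Two practical objections also stand. Analysis had begun when the article was written, so a more liberal rule adopted after results by arm were seen would itself be open to criticism. And Bonferroni has matching simultaneous confidence intervals, while Holm has no equally simple ones. The article promises no such intervals, so nothing it states would be lost.

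**Conclusion.** A free improvement. Holm over the same family gives the same familywise guarantee under the same assumptions and never rejects less. That follows from the procedures themselves and needs no assumption about the trial.

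The size of the gain does rest on assumptions. At d = 0.5 with the stated correlations and no dropout, the chance of showing an outcome's effect at all three weeks rises by 16 points with one outcome (32% to 48%), 15 with two (23% to 38%) and 10 with six (13% to 23%). The gain is smaller at d = 0.3 and d = 0.8, and dropout would lower all the power figures. Even with Holm the figure stays below 50% at d = 0.5, so the change does not make up for a limited sample size.

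**What to change.** Replace the Bonferroni sentence with wording such as: *Holm-adjusted p values will control familywise error at .05 over the between-arm comparisons*, followed by a list of the outcomes and weeks in that family. If the Bonferroni sentence was also meant for other comparisons, such as those within hypothesis 2a, say so and define that family separately.

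Record the date of the change and state that it was made without reference to results by arm. If that cannot be stated, label the Holm results as post hoc beside the Bonferroni ones.

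The cost is one or two sentences and no new data. Testing week 3 before weeks 6 and 9 may be considered separately, provided that the sponsor accepts the loss of power for effects that appear late.

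### The completer-versus-dropout t tests within each arm cannot show whether dropout biases the results: they are weak, and they do not examine the between-arm difference that would bias the arm contrast.

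*Protocol article*

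**What the plan says.** All of the following is in the protocol article, mostly in Data Collection, Management, and Analyses.

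- Arm sizes: "The intervention (n=50) and control (n=50) arms".
- Attrition check, planned in each arm: "additional independent *t* tests will compare seekers who provided data across all 4 time points with those who dropped out". The purpose given is "to ascertain if the sample with data across all 4 time points and the sample with fewer data points bias our results".
- Examples of dropout: seekers identified as high risk during the study, and threads that end because the befriender stops and the seeker does not continue with another.
- Missing data: "the Little Missing Completely at Random Test will address potential missing data via full information maximum likelihood imputation".
- Error rates, from the Results section: "with a significance level of .05 (95% reliability) and 80% power statistic".

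The article gives no expected dropout rate, does not name the variables to be compared, and does not say what follows from a significant or a non-significant attrition test.

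**The concern.** The article gives a specific test a specific inferential job, finding out whether incomplete data bias the results. Two features make the test unfit for it.

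First, the dropouts in an arm are a fraction of 50 people. A test with so few in one group has little chance of reaching significance at a moderate difference, so non-significance says little.

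Second, the trial's question is the contrast between arms. Completers who differ from dropouts to the same extent in both arms, with equal dropout, leave that contrast unshifted. A difference present in one arm only shifts it. Testing each arm on its own does not separate these cases.

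Unequal dropout is plausible here. According to Participants and Study Setting, arm 2 is wait-listed. During the comparison it therefore has no befriender threads, and the befriender-ended route that the article names can operate only in arm 1. At stake is whether the final report could cite a quiet attrition check as support for an unbiased arm comparison.

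**Working it through.** **Inputs from the article.** 50 per arm; alpha .05; "Independent-sample 2-tailed" for the arm comparison. Two-sided .05 is assumed for the attrition tests as well, because it is not restated for them.

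**Assumptions, not in the article.** Dropout of 10% to 40% per arm, equal in the two arms; a completer-dropout difference of d = 0.5 SD; and, in favour of the tests, that the score they compare shows the same difference as the outcome.

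**The plan's own figure.** No effect size accompanies the 50 per arm, so the sample size cannot be reproduced. Solved in reverse, 50 v 50 at two-sided .05 and 80% power corresponds to d = 0.566 (exact t). The article gives no power for the attrition tests.

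**Step 1: power of one within-arm test.** The noncentrality is d × √(n₁n₂/(n₁+n₂)) with 48 df. For 40 v 10 it is 0.5 × √(400/50) = 1.414. The pooled column uses the same formula with both group sizes doubled and 98 df.

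| Dropout | Completers v dropouts | Noncentrality | Power | Missed | Missed, arms pooled |
|---|---|---|---|---|---|
| 10% | 45 v 5 | 1.061 | 18% | 82.0% | 68% |
| 20% | 40 v 10 | 1.414 | 28% | 71.7% | 49% |
| 30% | 35 v 15 | 1.620 | 36% | 64.5% | 38% |
| 40% | 30 v 20 | 1.732 | 40% | 60.3% | 32% |

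Even at 50% dropout the within-arm miss rate is 59%. The difference that one within-arm test detects with 80% power is 1.35 SD at 10% dropout, 1.01 SD at 20% and 0.83 SD at 40%.

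**Step 2: what shifts the contrast.** Within an arm with dropout fraction p, the completers' mean differs from the mean of everyone randomised by p × d. The completers' arm contrast therefore shifts by p₁d₁ − p₂d₂. Neither within-arm test estimates this quantity.

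**Step 3: how the pair of tests behaves.** The arms are independent, so probabilities multiply. Write m for the miss rate in Step 1.

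- Difference in arm 1 only: shift = p × 0.5; both tests non-significant with probability m × 0.95.
- Same difference in both arms: shift = 0; at least one test significant with probability 1 − m².

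| Dropout | Arm 1 only: shift | Arm 1 only: both non-significant | Both arms: shift | Both arms: at least one significant |
|---|---|---|---|---|
| 20% | 0.20 × 0.5 = 0.10 SD | 0.717 × 0.95 = 68% | 0 | 1 − 0.717² = 49% |
| 30% | 0.30 × 0.5 = 0.15 SD | 0.645 × 0.95 = 61% | 0 | 1 − 0.645² = 58% |
| 40% | 0.40 × 0.5 = 0.20 SD | 0.603 × 0.95 = 57% | 0 | 1 − 0.603² = 64% |

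The check is silent more often than not when the contrast is shifted, and signals about half the time or more when it is not.

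**The case against.** Several stronger readings are tempting, and the document does not support them.

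- **A reader might infer that non-significance will clear the trial of bias.** The article states no such rule, no threshold and no consequence of either result. The most that follows is that a non-significant result could be misread in that way.
- **A reader might take 82% to 60% as the rate at which a biased trial passes the check.** It is the rate at which one test misses a within-arm difference, which is not itself bias in the arm contrast. The relevant figure in the arm-1-only case is 68% to 57%, and it too rests on assumed inputs.
- **A reader might take the 0.10 to 0.20 SD as the bias of the planned analysis.** It applies to a contrast among completers. The article also plans full information maximum likelihood, which uses the partial data of dropouts. Where dropout depends on recorded scores, such as an observed PHQ-9 result, it can reduce or remove the shift. It does not do so where dropout depends on scores that were never recorded. No bias figure under that method can be derived from the article.
- **A reader might infer that the Little test decides the missing-data method.** The article does not say so.

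It can also be said that sensitivity analyses and the choice of compared variables belong in an analysis plan that is not shown. That is right, and their absence alone is no finding. The point rests on a use of the t tests that the article states. The article also plans to follow up all seekers at weeks 6 and 9, which may limit dropout; Step 1 shows that fewer dropouts make the tests weaker.

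**Conclusion.** The concern stands in a limited form. Separate completer-versus-dropout t tests in arms of 50 cannot establish whether incomplete data bias the results. One reason is low power, at most about 40% for 0.5 SD over the assumed dropout range. The other is that they leave the between-arm difference unexamined. The low-power conclusion does not hinge on the dropout rate chosen, since the within-arm miss rate for 0.5 SD stays at 59% even at 50% dropout. It does depend on the 0.5 SD: differences of about 0.8 to 1.35 SD would be found with 80% power, depending on dropout. The shift figures further assume equal dropout fractions and a completers' contrast. Nothing here shows that the trial's results are biased, only that this check could not show that they are not.

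**What to change.** In Data Collection, Management, and Analyses:

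1. Describe the completer-versus-dropout comparison as descriptive, and state that its significance will not be used to judge bias.
2. Report the baseline completer-minus-dropout difference in each arm, and the difference of these two between arms, each with a 95% CI.
3. Judge the robustness of the week 3, 6 and 9 arm contrasts by a delta-adjusted sensitivity analysis on all 100 seekers. Shift the missing arm 1 scores for the worse over a prespecified range (for example up to 0.5 SD, which is an assumption for the sponsor to justify), and report the shift at which the conclusion changes.

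The Results section says that data collection is complete and analysis is in progress. The range should therefore be fixed before the arm contrasts are examined or, if that is no longer possible, labelled as chosen afterwards.

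The cost is some rewording and one further analysis on data already collected. The downside is that the report may have to say that dropout bias cannot be ruled out.
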